### Data collection and management

#### Plans for assessment and collection of outcomes

The primary efficacy indicator are ASM and Handgrip strength. The secondary outcome indicators encompass the abdominal muscle area and muscle density at the level of the third lumbar vertebra, including the rectus abdominis, transverse abdominis, internal and external obliques, quadratus lumborum, psoas major, and paraspinal muscles, which are quantified via QCT. Also included are 6-meter walking speed, the score of the FTSST, the score of the SPPB, calf/waist/hip circumference, serum irisin/myostatin. Considering the radiation from imaging examinations and the pain caused to patients by blood tests, the frequency and time of observation for each indicator are not completely the same, as detailed in Table 2.

**Table 2 tbl0002:** Time schedule for data collection of each indicator. (All abbreviations in the table are presented in "Abbreviations").

**No.**	**Indicators**	**baseline**	**Visit 1 (30 days after treatment)**	**Visit 2 (60 days after treatment)**	**Visit 3 (30 days after the end of treatment)**	**Visit 4 (90 days after the end of treatment)**
**1**	SARC—Calf	**√**	**√**	**√**	**√**	**√**
**2**	ASM	**√**		**√**		**√**
**3**	The abdominal muscle area and muscle density at the L3 level measured	**√**		**√**		**√**
**4**	Handgrip strength	**√**	**√**	**√**	**√**	**√**
**5**	6-meter walking speed	**√**	**√**	**√**	**√**	**√**
**6**	FTSST	**√**	**√**	**√**	**√**	**√**
**7**	SPPB	**√**	**√**	**√**	**√**	**√**
**8**	calf/waist/hip circumference	**√**	**√**	**√**	**√**	**√**
**9**	Srum irisin/Myostatin	**√**		**√**		**√**
**10**	routine blood test	**√**		**√**		**√**
**11**	blood glucose	**√**		**√**		**√**
**12**	hepatorenal function tests	**√**		**√**		**√**
**13**	ECG	**√**		**√**		**√**

#### Plans to promote participant retention and complete follow-up

Prior to the commencement of the study, all researchers will undergo training and be allocated tasks rationally. Each enrolled subject will be assigned to a fixed researcher, who will maintain contact with the subject throughout the entire study process and be responsible for treatment and all examinations. Given that elderly patients with SP may experience mobility impairments, we will make every effort to understand each patient’s health status, mobility capacity, and the distance from their residence to the hospital before enrollment to ensure the completion rate. Regarding transportation, we will provide three options for patients: 1. With the approval of the Ethics Committee, we will offer shuttle services to patients; 2. For patients who do not require shuttle services, we will provide an appropriate transportation allowance; 3. For individual patients with severe mobility limitations, we will dispatch medical staff to their homes to conduct acupuncture treatment and exercise guidance, subject to the approval of the Ethics Committee. One week before each examination and assessment, researchers will contact the participants to ensure their attendance on schedule. If a participant fails to attend the examination and assessment as scheduled, we will reschedule within one week to allow them to complete the process.

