#### Concealment mechanism

The computerized randomization program will not release the random codes until the patients are enrolled in the study, thus ensuring allocation concealment. Due to the differences in the operational methods between acupuncture and sham acupuncture, it is impossible to blind the researchers. However, the data collection and analysis will be completed by professional statisticians. The subjects and researchers will be unaware of the data, while the statisticians will be unaware of the study groups.

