### Assignment of interventions: Blinding

Due to the characteristics of the intervention study, in the design of the acupuncture intervention, blinding will not be applied to the subjects and researchers regarding the intervention measures. However, the data analysts will be blinded to the allocation of the intervention measures. The result evaluation and statistical analysis will be conducted by independent investigators who are unaware of the patient grouping.

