#### Data management

Clinical data will be collected and recorded by trained research assistants at our research center. The clinical examination data will first be entered into case report forms and then electronically input. Another technician will conduct a consistency check to ensure the accuracy of data entry. All data will be stored in password-protected computers. This study will be conducted in accordance with the Good Clinical Practice (GCP) to safeguard the rights, interests, and well-being of the participants, and to ensure that the collected data are complete and verifiable from the source documents. Patients can withdraw from the study at any time without giving any reason, and their medical care or legal rights will not be affected. After the completion of the study, the patient files will be retained for three years.

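### One unblinded researcher per patient is made responsible for both treatment and all examinations, which read literally conflicts with the blinded evaluation and leaves handgrip and the performance tests open to assessor bias

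*Protocol article*

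**What the plan says.** Four sections of the protocol article bear on who measures outcomes and what that person knows.

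- **Plans to promote participant retention and complete follow-up:** every patient gets one named member of the trial staff, "who will maintain contact with the subject throughout the entire study process and be responsible for treatment and all examinations".
- **Concealment mechanism:** because real and sham needling differ in technique, "it is impossible to blind the researchers". The same section says that "the data collection and analysis will be completed by professional statisticians".
- **Assignment of interventions: Blinding:** "blinding will not be applied to the subjects and researchers regarding the intervention measures". It then adds: "The result evaluation and statistical analysis will be conducted by independent investigators who are unaware of the patient grouping".
- **Data management:** "Clinical data will be collected and recorded by trained research assistants at our research center".

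The primary outcomes are appendicular muscle mass by DXA and handgrip strength. Table 2 schedules handgrip, 6-metre walk, five-times sit-to-stand (FTSST), SPPB and circumferences at baseline and at all four later visits.

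**The concern.** Whoever delivers the needling knows the arm. The real procedure is deep, seeks a needling sensation and is manipulated every 10 minutes. The sham is superficial, off-point and not manipulated. If that same person is also responsible for the examinations, the assessor is unblinded, whatever the blinding section promises.

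This matters most where the result depends on effort, encouragement or an observer's timing. Handgrip is a maximal voluntary contraction, scored as the better of two attempts. The walk and FTSST are timed, each scored on the best of three attempts, and the article allows a hand-held stopwatch for the gait part of SPPB. An assessor who knows the arm can influence these readings without meaning to. The sham arm is there to separate a specific effect from a placebo effect, and unblinded measurement weakens that separation on exactly these outcomes.

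**Working it through.** **Setting the sections side by side**

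1. The retention section gives treatment and all examinations to the same fixed researcher.
2. The concealment and blinding sections both say that researchers are not blinded to the intervention.
3. From 1 and 2, the person responsible for a patient's examinations knows that patient's arm.
4. The blinding section gives result evaluation to independent investigators who do not know the arm. There are two readings:
   - *Result evaluation includes measuring the outcome.* Then 3 and 4 cannot both be followed.
   - *Result evaluation means only assessing recorded data.* Then there is no conflict, but nothing in the article promises that measurements are taken blind.
5. On either reading, the text does not protect the measurements from an assessor who knows the arm.

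**Which outcomes are exposed**

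| Outcome | Role | Exposure |
|---|---|---|
| Handgrip | Primary | High: maximal effort, open to coaching |
| 6-metre walk, FTSST, SPPB | Secondary | High: effort and observer timing |
| Calf, waist and hip circumference | Secondary | Lower: tape placement and reading, no effort component |
| Muscle mass by DXA | Primary | Much lower |
| QCT at L3, serum irisin and myostatin by ELISA | Secondary | Much lower |

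**The plan's own figure**

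The article gives no figure for assessor bias. Its one calculation is the sample size for muscle mass. With SD 0.80 and difference 0.68, two-sided 5%, the stated formula gives 2 × (1.960 + 1.645)² × 0.80² / 0.68² = 35.97, so 36 per group. This matches the stated 36 at 95% power, a power the article does not state. Then 36 / 0.9 = 40. The present point does not depend on this calculation.

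**Illustration of size (the bias is assumed)**

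Inputs from the article: 240 patients in total, 1:1, so 120 per arm; 10% dropout, so 120 × 0.9 = 108 per arm; two-sided 5% test. Assumed: no true effect, and unblinded assessment shifts the between-arm difference by b standard deviations.

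Noncentrality = b / √(2/n). The rejection probability is P(Z > 1.96 − nc) + P(Z < −1.96 − nc).

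For b = 0.2 and n = 108: 0.2 / √(2/108) = 1.47, and the probability is about 0.31.

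| Assumed shift | 108 per arm | 120 per arm |
|---|---|---|
| 0.1 SD | 11% | 12% |
| 0.2 SD | 31% | 34% |
| 0.3 SD | 60% | 64% |
| 0.4 SD | 84% | 87% |

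The nominal rate is 5%. The 120-per-arm column is the higher one: more patients tighten the interval around the biased value and do not remove the bias.

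**The case against.** **The word is responsible, not performs.** A reader might infer that the treating researcher personally carries out every examination. The article does not say so. The sentence sits in a section about contact, transport and rescheduling, and all examinations would include DXA, QCT, ECG and blood tests. Elsewhere an acupuncturist needles, a doctor supervises exercise and research assistants record data. A case-manager role is therefore possible. This limits how firmly the point can be put. It does not remove it, because no section states that role and the sentence treats examinations exactly as it treats treatment.

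**The blinding section may govern.** If so, the fault is one loose phrase in the retention section. That is fair, but a site reading both sections has no rule telling it which prevails.

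**The other two sections may not conflict.** A reader might infer that statisticians and research assistants are two further rival assessors. The data management section goes on to case report forms, data entry and consistency checks, and the concealment section pairs collection with analysis. Both may concern recorded data only, so they call for clarification and are not proof of further contradiction.

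**The size is assumed.** Neither a bias nor a handgrip SD is in the article. No single rejection rate, such as 31%, can be presented as the trial's error rate. Only the range is informative. An electronic dynamometer also limits reading error, though not coaching.

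**Patients are unblinded too.** They may vary their own effort or tell the assessor their arm, so a blinded assessor is only a partial remedy. This stands as a limit on what the fix can achieve.

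**Conclusion.** The concern holds in a limited form. Read literally, the retention section conflicts with the blinding section. Read narrowly, the blinding section promises no blinded measurement. Both readings leave one of the two primary outcomes (handgrip) and three secondary performance tests open to assessor bias, with circumferences exposed to a lesser degree and DXA, QCT and ELISA much less.

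The documents do not establish that unblinded staff will in fact take these measurements, or how large any bias would be. The 11% to 84% range rests on assumed shifts of 0.1 to 0.4 SD, no true effect and 108 per arm. It shows that modest shifts would matter at this sample size. It does not predict them.

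This is not detail left to an analysis plan: the article states the rule, and following it gives a worse result. The protocol validation section says that outcome assessment had not yet been reached, so as of that statement later measurements could still be protected. Readings taken unblinded cannot be corrected in the analysis.

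**What to change.** 1. In the retention section, delete the words *and all examinations*, so that the fixed researcher keeps contact and treatment only.
2. In the blinding section, state that handgrip, 6-metre walk, FTSST, SPPB and circumferences are measured by the independent evaluators already named there. They should deliver neither acupuncture nor sham to anyone in the trial and have no access to the allocation. Exchanging patients among treating colleagues would not secure this.
3. Use a standard script for the effort-dependent tests, and ask patients not to tell the assessor which treatment they receive.
4. In the concealment and data management sections, make clear that statisticians and research assistants handle recorded data, or bring both sections into line with this rule.
5. State as a limitation that expectation effects remain because patients are unblinded.

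**Cost:** protocol wording and visit rostering so that treating and assessing staff are separate. The blinding section already commits to independent evaluators, but the article gives no staffing figures, so whether extra staff are needed at a site cannot be judged from it.

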#### Data management

Clinical data will be collected and recorded by trained research assistants at our research center. The clinical examination data will first be entered into case report forms and then electronically input. Another technician will conduct a consistency check to ensure the accuracy of data entry. All data will be stored in password-protected computers. This study will be conducted in accordance with the Good Clinical Practice (GCP) to safeguard the rights, interests, and well-being of the participants, and to ensure that the collected data are complete and verifiable from the source documents. Patients can withdraw from the study at any time without giving any reason, and their medical care or legal rights will not be affected. After the completion of the study, the patient files will be retained for three years.

#### Confidentiality

All records containing personal information will be stored separately in a database and shared solely for research purposes within the scope of this study. Only healthcare professionals and researchers have the right to access the information required to carry out the interventions.

#### Plans for collection, laboratory evaluation and storage of biological specimens for genetic or molecular analysis in this trial/future use

Blood samples will be collected at the three research centers for evaluation purposes. Once the samples reach the local research laboratories at each center, collection, transportation, storage, and preparation will be carried out in accordance with local protocols. Prior to being processed within the specified time, the blood samples need to be stored at a temperature range of 2 - 8 °C. All samples collected during the trial will be labeled with patient identification codes and will not contain any identifiable data. Patients have the option to consent to the retention of their samples for future research use. The samples will be stored anonymously in a central location. After the completion of the study, they will be preserved for a minimum of 5 years and a maximum of 10 years, and then these specimens will be destroyed by incineration according to local guidelines and protocols. The potential uses of the stored samples have been included in the informed consent form. However, any further use of the samples still requires the approval of the institutional ethics committee.

### Statistical methods

#### Statistical methods for primary and secondary outcomes

The main efficacy indicators will be analyzed using both the full analysis set (FAS) and per protocol set (PPS). The other efficacy indicators will be analyzed via the FAS set, while the safety indicators will be analyzed with the safety set (SS). The baseline equilibrium analysis will also be carried out using the FAS set.

Statistical analysis encompasses statistical description and statistical inference. For the statistical description of quantitative indicators, it includes mean, standard deviation, median, minimum value, and maximum value. Qualitative indicators are depicted by frequency tables and constituent ratios. Statistical inference involves interval estimation and hypothesis testing. For quantitative indicators, their two-sided 95 % confidence intervals (CIs) will be estimated. Each efficacy indicator will undergo bilateral testing with a significance level of α = 5 %. The null hypothesis posits that there is no statistically significant difference between the test group and the control group, whereas the alternative hypothesis contends that there is a statistically significant difference between the two groups. When *p* < 0.05, the null hypothesis will be rejected, and the difference between the two groups is deemed statistically significant.

Regarding measurement data, normality analysis is performed first. All data conforming to normal distribution are expressed as mean ± standard deviation. For comparison within the same group before and after treatment, the paired *t*-test is utilized, and for comparison between groups, the independent samples *t*-test is employed. For non-normally distributed measurement data, the rank sum test is adopted. For non-graded data in count data, the chi-square or non-parametric test is used. For graded data, the Ridit test is applied. In a bilateral test, a P value <0.05 is considered as a statistically significant difference.

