### Trial design

This study is a prospective, multi-center, parallel-group randomized controlled trial, which is a superiority intervention study. SP patients who meet the diagnosis and inclusion criteria will be recruited. Patients will be randomly assigned to two groups in a 1:1 ratio: the acupuncture group (receiving acupuncture at selected points combined with exercise therapy) and the sham acupuncture group (receiving sham acupuncture combined with exercise therapy). Both groups will be treated for 60 days and followed up for 90 days. Various efficacy indicators and safety indicators of the patients will be recorded before treatment, at 30 days of treatment, at 60 days of treatment, 60 days after the end of treatment, and 90 days after the end of treatment. After randomization, the Clinical Study Coordinator(CRC) will schedule treatment sessions. All recruitment procedures would be documented in the log file.This trial protocol uses the Standard Protocol Items :Recommendations for Interventional Trials (SPIRIT) reporting guidance [26]. Fig. 1 shows a flow chart of the study design.

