### Sample size

Regarding the design of the sample size calculation formula, we referred to the 8th edition of "Epidemiology" published by the People's Health Publishing House [27]. The formula is presented as follows: *N* = 2(Z₁₋α/₂ + Zβ)²σ²/d². In this formula, Z₁₋α/₂ represents the value corresponding to the first type of error probability, and Zβ denotes the value for the second type of error probability. σ is the standard deviation estimated through literature study [[17], [18], [19], [20], [21], [22], [23], [24], [25]], with σ=0.80 kg/m². d is the difference between the means of the two groups as estimated through literature study [[17], [18], [19], [20], [21], [22], [23], [24], [25]]. The mean value was 6.76 kg/m² in the acupuncture group and 6.08 kg/m² in the sham acupuncture group, thus *d* = 0.68 kg/m². Substituting the above data into the formula yields a sample size of 36 cases per group. Considering a 10 % dropout rate, the number of cases to be included in each group should be no <40. Since a 1:1 ratio is employed for both groups, 80 cases are needed at each center, totaling 240 cases.

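### Two primary endpoints are each tested at an unadjusted two-sided 5%, with no primary visit and no either/both rule, so an overall 5% error rate is not protected

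*Protocol article*

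**What the plan says.** All references are to the protocol article.

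- **Two primaries.** Plans for assessment and collection of outcomes states: "The primary efficacy indicator are ASM and Handgrip strength". The Primary efficacy indicator section lists the same two.
- **Alpha and rejection rule.** Statistical methods for primary and secondary outcomes states: "Each efficacy indicator will undergo bilateral testing with a significance level of α = 5" per cent. The same section ends: "In a bilateral test, a P value <0.05 is considered as a statistically significant difference".
- **Test.** "for comparison between groups, the independent samples *t*-test is employed", with a rank sum test for non-normal data. No visit is attached to the test.
- **Visits.** The Trial design section gives the assessment times, the last two counted from when therapy stops: "before treatment, at 30 days of treatment, at 60 days of treatment, 60 days after the end of treatment, and 90 days after the end". The outcomes section adds that "the frequency and time of observation for each indicator are not completely the same, as detailed in Table 2". Table 2 and the Participant timeline grid both schedule ASM at Visits 2 and 4, and handgrip at Visits 1 to 4.
- **Analysis sets.** "The main efficacy indicators will be analyzed using both the full analysis set (FAS) and per protocol set (PPS"). The section on non-adherence and missing data gives ITT precedence for interpretation and reports per-protocol results for comparison.
- **Sample size.** It rests on muscle mass alone: "The mean value was 6.76 kg/m² in the acupuncture group and 6.08 kg/m² in the sham acupuncture group", with an SD of 0.80 kg/m². Handgrip has no calculation.

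**The concern.** This is a superiority trial with two primary endpoints. The alpha rule applies the full 5% to each indicator separately. Nothing links the two tests: there is no split, no hierarchy, and no statement on whether one or both must be positive. No visit is singled out either, so ASM has two candidate post-baseline comparisons and handgrip has four.

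A trial report could follow this text to the letter and rest its efficacy claim on whichever primary, at whichever visit, fell below 0.05. The real error rate of that claim would be above 5%, and the choice of endpoint and visit could be made after the results are seen. Prespecification matters more here because the Blinding section says that subjects and researchers are not blinded to the intervention.

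**Working it through.** **Inputs.** From the document: two-sided 5% per indicator; two primaries; ASM at 2 and handgrip at 4 post-baseline visits, so 2 + 4 = 6 endpoint-by-visit comparisons over four visits; SD 0.80 and difference 6.76 − 6.08 = 0.68 kg/m²; 10% dropout; 240 patients at 1:1, so 120 per arm. Not in the document: any correlation between endpoints or visits, and the power. Correlations are assumed over a range below.

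**The plan's own figure.** n per group = 2(z₁₋α/₂ + z_β)²σ²/d². At two-sided 5% and 95% power: 2 × (1.960 + 1.645)² × 0.80²/0.68² = 35.97, so 36. That matches the stated 36, and 36/0.90 = 40. Power is inferred, since 80% gives 22 and 90% gives 30. The stated size therefore corresponds to one endpoint at an unsplit 5%.

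**Either primary counts, one fixed visit.**
- Independent: 1 − 0.95² = 9.75% (upper bound 2 × 5% = 10%).
- Assumed correlation 0.3, 0.5, 0.7 (bivariate normal simulation, 500,000 draws): 9.6%, 9.1%, 8.3%.

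**Any of the six comparisons counts.**
- Independent: 1 − 0.95⁶ = 26.5% (upper bound 30%).
- Correlated (same simulation method, common correlation between visits within an endpoint, and a common correlation across endpoints):

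| Within-endpoint | Cross-endpoint | Familywise error |
|---|---|---|
| 0.5 | 0 to 0.25 | 23.3% to 22.5% |
| 0.7 | 0 to 0.35 | 20.3% to 19.4% |
| 0.8 | 0 to 0.40 | 18.3% to 17.3% |
| 0.9 | 0 to 0.45 | 15.8% to 14.7% |

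**Both primaries must succeed, one fixed visit.** Whenever at least one null hypothesis is true, rejecting both requires rejecting that one, which has probability at most 5%.

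**After splitting alpha.** Two tests at 0.025 give 1 − 0.975² = 4.94% if independent, and at most 5% under any correlation. Holm has the same 5% bound.

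**Cost in power for ASM.** Evaluable per arm: 120 × 0.90 = 108. Detectable difference at 90% power:
- alpha 0.05: (1.960 + 1.282) × 0.80 × √(2/108) = 0.35 kg/m²
- alpha 0.025: (2.241 + 1.282) × 0.80 × √(2/108) = 0.38 kg/m²

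Both are well below the planned 0.68, and power at 0.68 stays above 99.9%. Handgrip power cannot be computed, because no inputs are given.

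**The case against.** The strongest reply is that the inflation is conditional. The statistical methods section says when a difference on an indicator is significant. It does not say that one significant indicator makes the trial positive, or that each visit gets its own between-group test. The missing primary visit and success rule are silences in a condensed article, and an analysis plan that is not shown may fill them. This stands as a limit on the size: the six-comparison figures apply only if any visit may count. It does not remove the point. The text affirmatively fixes a full 5% for each indicator while naming two as primary, so an analysis plan that splits alpha would have to override it.

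Three stronger readings are tempting, and the document does not support them:
- A reader might infer that the error rate simply is 10% to 26%. The upper figure needs independent tests, which repeated measurements on the same patients are not, and the whole range needs an any-success rule that is nowhere stated.
- A reader might count six post-baseline visits. There are four; six is the number of endpoint-by-visit comparisons.
- A reader might add further inflation for analysing both FAS and PPS. The plan already lets ITT lead, with per-protocol results reported for comparison.

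That the sample size covers muscle mass only is a matter of power for handgrip and is no evidence of type I error inflation.

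**Conclusion.** The point holds in this form: as written, the plan does not protect an overall 5% error rate for its efficacy claim. The rate runs from at most 5% under a both-must-succeed rule at one visit, to about 8% to 10% if either primary suffices at one visit, to roughly 15% to 23% if any of the six comparisons may count. The independence values are 9.75% and 26.5%. The first range assumes a between-endpoint correlation from 0 to 0.7. The second assumes within-endpoint correlations of 0.5 to 0.9 and cross-endpoint correlations of 0 to 0.45. Which figure applies cannot be settled from the document, because it states no success rule. That gap, alongside an explicit 5% for each indicator, is what needs correcting.

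**What to change.** Before outcome data are examined, amend the statistical methods section as follows:

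1. Name Visit 2 (60 days, end of treatment) as the primary time point. It is the first visit at which both primaries are measured, and its timing agrees across the Trial design section, the Participant timeline and Table 2.
2. Test ASM and handgrip at that visit in the ITT/FAS set with Holm at an overall two-sided 5%: the smaller p-value against 0.025, then the other against 0.05. Claim efficacy only for an endpoint that passes.
3. Label all other visits as supportive.

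An explicit both-must-succeed rule, or a fixed testing order at that visit, would also control the error. What matters is that one rule is written down.

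The follow-up visits need reconciling in the same amendment. After the end of treatment they fall at 60 and 90 days in Trial design, 30 and 60 days in the Participant timeline note, and 30 and 90 days in Table 2.

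**Cost.** The smaller p-value must fall below 0.025, which moves the detectable ASM difference from 0.35 to 0.38 kg/m²; ASM needs no extra patients. The 5% rule sits in the protocol, so the change needs funding-committee and ethics approval and notice to subjects under the article's amendment section. The Protocol validation section says that recruitment and treatment are under way but outcome assessment has not been reached, so the rule can still be credibly prespecified.

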### Outcomes

#### Primary efficacy indicator

(1)The Appendicular Skeletal Muscle Mass: Both the Asian Working Group for Sarcopenia and the European Working Group on SP in Older People have mentioned that ASM measured by DXA is an important index for the diagnosis and efficacy evaluation of sarcopenia, which can directly reflect the changes in muscle mass [1,2]. A value of <7.0 kg/m^2^ in men and <5.4 kg/m^2^ in women is considered positive.(2)Handgrip strength: Handgrip strength is an important indicator for measuring muscle strength and one of the diagnostic criteria for SP. We use an electronic digital grip dynamometer. The patient stands with the elbow extended, and the dominant hand performs an isometric contraction with maximum force. The measurement is taken twice on the same hand with an interval of at least 15 s, and the maximum reading (kg) is selected. By referring to the recommendations of the Asian Working Group for Sarcopenia, we set the threshold as <28 kg for men and <18 kg for women [1].

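### The group comparison is an unadjusted t-test or rank-sum test chosen by a normality check, so baseline, sex and centre are left unused and precision is lost, though validity is not

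*Protocol article*

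**What the plan says.** The Protocol article, section Statistical methods for primary and secondary outcomes, sets one rule for every continuous outcome. It begins with a check on the data: "Regarding measurement data, normality analysis is performed first". If normality is accepted, the rule between arms is that "for comparison between groups, the independent samples *t*-test is employed". Changes inside each arm get a test of their own: "For comparison within the same group before and after treatment, the paired *t*-test is utilized". If normality is not accepted, "For non-normally distributed measurement data, the rank sum test is adopted". The same section promises two-sided 95% confidence intervals for quantitative indicators.

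Neither that section nor the ones after it on additional analyses and missing data names a covariate or a regression model. Baseline is used only for a balance check and in the within-arm paired tests. The text does not say whether the between-group test takes final values or changes from baseline.

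Other sections supply the context:

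- Plans for assessment and collection of outcomes: "The primary efficacy indicator are ASM and Handgrip strength". Table 2 there schedules both at baseline.
- Inclusion criteria: both sexes are eligible.
- Primary efficacy indicator: the cut-offs are sex-specific, 7.0 and 5.4 kg/m² for ASM; for grip, "we set the threshold as <28 kg for men and <18 kg for women".
- Study setting and Sequence generation: three centres, complete randomisation, no stratification described.

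**The concern.** Muscle mass and grip strength differ between patients mainly for reasons that exist before treatment starts. A test that ignores the baseline value and sex leaves those differences as noise. Because allocation is not stratified, nothing in the design evens out sex or centre between arms, and nothing in the analysis allows for an uneven split.

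Two features add to this. First, the normality check lets the outcome data choose the test, and with it the quantity being assessed: a mean difference or a rank comparison. A promised confidence interval for a mean difference would not match a rank-sum p-value. Second, both arms do the same supervised resistance exercise, so both may improve. A within-arm p-value therefore says nothing about what acupuncture adds.

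At stake are the width of the interval around the treatment effect, the ability to detect effects smaller than the planning value, and the clarity of the report.

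**Working it through.** **Inputs from the Protocol article (Sample size).** SD 0.80 kg/m²; difference 6.76 − 6.08 = 0.68 kg/m²; 36 per group; 10% dropout; 80 per centre, 240 in total. That is 120 per arm randomised and 120 × 0.9 = 108 evaluable.

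**Assumed.** The baseline-outcome correlation r is not given; the range 0.6 to 0.9 is shown. The SD is taken as equal at baseline and follow-up.

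**Step 1: the plan's own figure.** n = 2(Z₁₋α/₂ + Zβ)²σ²/d². With two-sided 5% and 95% power, 2 × (1.960 + 1.645)² × 0.64/0.4624 = 35.97, so 36 per group. Then 36/0.9 = 40, and 80 × 3 = 240. The power is not stated; 95% is the value that returns 36 (90% returns 30).

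**Step 2: the unadjusted test on final values.** SE = 0.80 × √(2/108) = 0.109. Power for 0.68 exceeds 99.9%. The difference detectable with 90% power is 0.109 × (1.960 + 1.282) = 0.353 kg/m². Power for a true 0.25 kg/m² is 63%.

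**Step 3: the alternatives.** Relative to final values, the variance is multiplied by 2(1 − r) for change scores and by 1 − r² for ANCOVA. The ratio of ANCOVA to change-score variance is (1 − r²)/[2(1 − r)] = (1 + r)/2.

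| r | Detectable at 90% power: final values | Changes | ANCOVA | ANCOVA interval narrower than final values | ANCOVA interval narrower than changes | Power for 0.25 kg/m², ANCOVA |
|---|---|---|---|---|---|---|
| 0.6 | 0.35 | 0.32 | 0.28 | 20% | 11% | 82% |
| 0.7 | 0.35 | 0.27 | 0.25 | 29% | 8% | 90% |
| 0.8 | 0.35 | 0.22 | 0.21 | 40% | 5% | 97% |
| 0.9 | 0.35 | 0.16 | 0.15 | 56% | 3% | over 99% |

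For example, at r = 0.6, √0.64 = 0.80, so the interval is 20% narrower than for final values, and 0.353 × 0.80 = 0.28. Against changes, √0.80 = 0.894, so it is 11% narrower. The percentages apply to grip at its own r; the article gives no grip SD, so there is no figure in kg.

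**Step 4: the pre-test rule.** A simulation of 3,000 trials per setting used 108 per arm, half women, a sex gap of 1.6 kg/m², within-sex SD 0.5 and r = 0.8. Under no effect, the pre-tested rule rejected in 5.7% of trials, the plain t-test in 5.5% and ANCOVA in 5.0%. Normality was rejected in about 99% of trials because two sexes were mixed. This is illustrative only: the assumed total SD is √(0.64 + 0.25) = 0.94, above the planned 0.80, so its power results are not used here.

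**Step 5: within-arm tests.** Suppose both arms have the same true change c. With SD 0.80 and r = 0.8, the SD of a change is 0.80 × √0.4 = 0.506 and its SE is 0.506/√108 = 0.0487. The chance of significance in one arm is 0.537 at c = 0.10 and 0.869 at c = 0.15. Exactly one arm is then significant with probability 2 × 0.537 × 0.463 = 50% and 2 × 0.869 × 0.131 = 23%. At c = 0.20 it is 3%.

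**The case against.** The strongest reply is that nothing here is invalid. The unadjusted test is unbiased under randomisation, the choice between t-test and rank-sum test is written down in advance, the simulated error rate stays near 5%, and power for the stated target is ample. Covariate detail is also often left to a fuller document. The validity point stands in full. The last point does not: the article states its method, and that method has no covariate.

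Four stronger readings are tempting and are not supported:

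- *The planning means of 6.76 and 6.08 show that raw final values are compared.* They are literature values with no time point, and the statistical section is silent. If changes are compared, much of the gain has already been secured.
- *The sex gap explains the whole planning SD.* At half men, a gap of 1.6 kg/m² gives a between-sex SD of 1.6 × √0.25 = 0.80, which would leave no variation within sex. The gaps of 1.6 kg/m² and 10 kg are diagnostic thresholds, not mean differences. They show that sex matters, not by how much.
- *Chance sex imbalance adds a further error.* On that same proxy, one SD of imbalance at 120 per arm is √(0.25 × 2/120) = 0.0645, and × 1.6 gives 0.10 kg/m². The unadjusted SE is 0.80 × √(2/120) = 0.103, so the interval already contains this. It is avoidable noise, not an extra penalty. A constant sex offset would also cancel in changes.
- *Superiority rests on the paired tests.* The hypotheses in the article compare the two groups; the paired tests are supplementary, and the risk is one of misreading.

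The gains from baseline and from sex also overlap, since part of r in a mixed-sex sample is sex itself. They should not be added together.

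**Conclusion.** The point holds as a matter of efficiency and clear reporting. For any r, ANCOVA is at least as precise as either reading of the stated test, apart from the few degrees of freedom spent on covariates. At 108 evaluable per arm and SD 0.80, the ASM difference detectable with 90% power falls from about 0.35 kg/m² to between 0.28 and 0.15 for assumed r of 0.6 to 0.9 if final values are compared. If changes are compared, the further gain is small. The article does not settle which reading applies, and that is itself a gap in a stated method.

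The value of adjusting for centre cannot be quantified, because no between-centre variance is given. The data-driven choice of test and the within-arm p-values are worth removing on either reading. A reader should not conclude that the planned test is biased or that the trial is underpowered for 0.68 kg/m².

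**What to change.** Make the primary between-group analysis of ASM and of handgrip an ANCOVA of the post-treatment value on treatment, baseline value, sex and centre. Fit it at the primary time point the sponsor designates (day 60 is the end of treatment), whatever a normality test shows, and report the adjusted difference with its 95% confidence interval. Keep the rank-sum test as a sensitivity analysis. Use the same model for continuous secondary outcomes. Present within-arm changes descriptively, without p-values.

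The cost is wording in the analysis section. Baseline values, sex and centre are already available, so no patients, visits or measurements are added. The section Protocol validation reports that outcome assessment has not been reached, so the change can still be made before outcomes are seen.
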